## 4 Experimental paradigm

Analyzing children's behavior in natural settings is the most ecologically valid method of assessing how they build social bonds (Elliott and Gresham, 1987). Consequently, the methodology we propose involves a combination of familiar tasks, comprising hypothesis construction and free discussion. A videoconference setup will include a camera and high-quality microphone, allowing us to collect high-fidelity video and audio during the entire course of the experiment (Figure 2A), that we can then analyze (in large part automatically). Our data analysis pipeline uses new methods for allying the multiple streams of data: verbal, non-verbal and paraverbal behaviors in conversation, levels of rapport, task performance, and IBS.

### 4.1 Target population and sample

An *a priori* power analysis was conducted using G^*^Power 3.1.9.7 (Faul et al., 2007) to determine the sample size needed for the study. The analysis was based on an ANOVA with 4 age groups and 6 measurements, using an effect size of (d = 0.24), based on our pilot study results, and an alpha of 0.05. The results indicate that a total sample size of 176 dyads will be required to achieve a power of 0.95. This aligns with the recommendation of Bizzego et al. (2022), who suggested a minimum sample size of *N* = 150 to detect significant IBS. There are significant challenges in recruiting participants for hyperscanning experiments, and particularly for recruiting dyads of unfamiliar children. In the event of a smaller sample size, we can adopt an analytical approach, such as the non-parametric bootstrap test with a pooled resampling method, as proposed by Dwivedi et al. (2017), and cited in Bizzego et al. (2022), which has demonstrated satisfactory performance in cases of small sample sizes and non-normally distributed data. We will enlist equal numbers of dyads from 4 age groups: 5–6, 7–8, 9–10, and 11–12 years (44 dyads per group). As social interaction may differ between boys and girls at these ages (Underwood et al., 1999), dyads will be of the same gender (both boys or both girls), and half of our participants will be male and half female (88 dyads of girls and 88 dyads of boys). As described above, in order to assess the initial building of rapport, all children will be strangers to one another. Our videoconference set-up will facilitate this, as we will set up video-conferencing in 2 different schools or after-school programs.

### 4.2 Task description

Adducing evidence for the claims outlined above places a number of constraints on the kind of task we can use: in order to investigate neural synchrony during collaboration, the task must allow both a solo and collaborative mode, so that we can compare IBS between the two and ensure that it is not due to looking at the same stimuli (Hasson et al., 2008). The task also needs to encourage social exchange, as well as to be engaging for children in a quite wide age-range (5–12 years old). In order to measure performance, the task must have answers–either tasks with correct answers, or where the nature of answers can be assessed. The age of the participants indicates that they will have a relatively short attention span, meaning that the task must be able to be completed relatively rapidly. On the other hand, since a relatively rapid task may not give enough time for rapport to develop, we have designed a longitudinal component, whereby participants engage in slightly different but comparable tasks, spending 2 weeks on each of three tasks, for a total of 6 weeks, as we have done in prior research (Finkelstein, 2018; Madaio et al., 2018; Cassell, 2022). In order to collect high-fidelity data, the task needs to be displayed on the external screen in front of the child (rather than on a piece of cardboard laid on a table, for example) so that the child's face and body are oriented toward a webcam and microphone placed next to the monitor (the computer and keyboard will be located elsewhere to diminish distractions). Finally, because a subsequent study will integrate an AI learning companion that is based on optimal performance in the child-child task, the task must allow a virtual peer agent to collaborate with the child, as well as allowing two real children to participate.

Keeping all of these constraints in mind, we therefore designed a relatively simple paradigm: a set of three tasks (described below) that ask children to generate hypotheses and evidence for their hypotheses. The children work on each of the three tasks for 2 weeks, meaning that the entire study takes 6 weeks.

Specifically, in the first, solo, phase the children will be asked to describe out loud as much evidence as they can muster for claims they are making. While this kind of task may sound too scientific for 5–6 year old children, a significant body of literature describes children's ability to do just this, albeit without necessarily using the words “hypothesis” or “evidence” (Sodian et al., 1991; Ruffman et al., 1993). Indeed, requesting scientific thinking of this sort is a common style of educational activity for the entire age group. If the participants are still generating answers at 8 min they will be encouraged to wrap up, and after 10 min they will be stopped.

Next the children will be invited to collaborate by sharing their ideas with the other child in the dyad, in order to come up with a final list of claims and evidence for those claims that they will later present to an experimenter.

After the collaboration phase, the children will engage in a social phase, where they will be asked to chat with one another in free discussion for 8–10 min while the experimenters “get their paperwork together”.

After the social phase, we will turn off the children's cameras and ask them to self-report their feelings of closeness to the other child in two ways: first by rating their level of preferred closeness to the other child in the dyad, using a well-validated preferred closeness scale for children (Strayer and Roberts, 1997), and then by completing their feelings of closeness using the “Inclusion of Other in Self” (IOS) scale (Aron et al., 1992; adapted for children by Rabinowitch and Knafo-Noam, 2015). They will then present their task results to an experimenter located locally in each of the two venues, for no more than 8–10 min. The experimenter will give no feedback other than continuation markers such as “uh huh”. This phase will serve to assess the children's learning gains after each week. Figure 1 summarizes the experimental paradigm.

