## 1 Introduction

Understanding how we learn to form social bonds with others, and the roles that building of social bonds plays in our life, holds significant value as it promises to unveil the intricate processes through which individuals connect, form meaningful relationships, and cultivate a sense of belonging, ultimately contributing to personal wellbeing, societal cohesion, and the overall fabric of social interaction. As well as its importance in and of itself, connections with those around us also play a significant role in task performance where, for example, collaboration is improved when friends work together (Sainsbury and Walker, 2009). However, the picture is not all rosy, increasing even further the need to understand. While a significant literature demonstrates that when students feel a connection to their peers they learn more (Clark and Dumas, 2015; Madaio et al., 2018), there is also a literature demonstrating that some students may put so much energy into building a relationship with their peers, that they neglect the schoolwork on which they are supposed to collaborate. This is particularly the case for low-performing students, who may wish to distract their peers from collaborative work in order to avoid engaging in tasks they do not enjoy or do well (Godwin et al., 2016).

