***Claim 1: Conjunctions of conversational behaviors across modalities better***
***predict IBS*. **Understanding how social bonds among peers are reflected in IBS requires the integration across the conversational modalities: verbal, non-verbal, and paraverbal, rather than looking at one single conversational modality or behavior (such as eye gaze).***Claim 2: IBS and rapport evolve similarly across time*. **We use Dynamic Time Warping to quantify the temporal similarity between the two representations of social connectedness, through dyadic measures at the neural and psychological level.***Claim 3: IBS Granger-causes reciprocal conversational behaviors*. **Beyond temporal similarity, we expect that IBS is a precondition of successful dyadic conversational behavior and thus the emergence of rapport.***Claim 4: Not all rapport is productive*. **We introduce the notion of “productive rapport”; that is, rapport that leads to learning gains in educational tasks, in contrast to unproductive rapport that is detrimental to learning. We therefore run analyses that examine whether there is a inverted U-shaped curve between rapport-building and performance.***Claim 5: Rapport-building is a process that takes time*. **Rapport is rarely built in a 1-h session, and so we argue that a study design must illuminate the time course of rapport at both the time scale of an hour during a single interaction, and of several weeks in a longitudinal design.***Claim 6: Brain regions evolve with age*. **It is well-known that the brain evolves across the period of middle childhood and beyond (Lebel and Beaulieu, 2011). We argue that with age we will find more reciprocal conversational behaviors, as children become more able to participate in interpersonal synchrony, and increasingly able to develop abstract shared mental representations with others. We predict that this will lead to greater IBS, and a progressive shift in activation from rTPJ to PFC.

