### 5.5 Educational performance

We argue for two types of rapport to be distinguished: productive and unproductive. Both types are associated with important health and wellbeing benefits, such as feelings of social cohesion. However, we define productive rapport as that which serves not only to improve wellbeing, but also to increase learning gains when two children collaborate. Unproductive rapport, on the other hand, may serve to distract the learners and reduce learning gains. To assess what behaviors identify productive rapport, we will assess the learning gains of the individuals in each dyad, and the mean learning gain of the dyad, each week and over the period of the 6 weeks, as follows: as described above, the children will individually report their hypotheses and evidence to a locally-located experimenter each week, after the collaborative and free discussion phases are finished. This “reporting out” serves as a metric of performance on each week's work. In addition, the delta between a pre-test (before the 6 weeks begin) and post-test (after the end of the 6^th^ week) will measure learning gains over the course of the 6 weeks for each individual and for the dyad in order to assess the relationship between IBS, use of conversational behaviors, level of rapport, and learning gains. The pre-test and post-test will be similar to the first task used in week 1 and 2, and they will be administered by the experimenter located in each venue. Here the experimenter will show the child an image of a new imaginary animal (a different animal for the pre-test than for the post-test), and several pictures of environments, and ask the child whether each of the environments would be a good or bad place for the animal to live in and why. After the child has given arguments for why each of the environments would be suitable or unsuitable for the imaginary creature, the experimenter will ask which of the environments would be best and why. Once again this will last no more than 8–10 min. The students' responses on the weekly read-out and the pre- and post-test will be annotated for instances of every-day science reasoning language (hypotheses, claims and evidence, expressed in lay language, such as “I *think that* he can climb trees *because* he has long claws”). The annotation will be carried out using a scoring manual for everyday science language that we developed for prior work (Finkelstein et al., 2013; Finkelstein, 2018), and that has achieved high inter-rater reliability. The manual was developed based on a significant body of prior work (*inter alia*, Lemke, 1990; Kafai and Ching, 2001; Kurth et al., 2002; Nemirovsky et al., 2004). The categories include “testing or evaluating ideas”, “causation”, “explanation”, sorting/classifying”, and “comparing”, among others. The children's interactions with one another, both during the collaboration phase and the social phase are also annotated for conversational behaviors and for rapport, as described below.

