### 6.4 Claim 4: not all rapport is productive: adding in performance data

While rapport is often seen as beneficial in general, and in particular for collaborative tasks, its impact on task performance is not uniformly positive. To investigate this, we propose integrating performance data into our analysis of IBS, conversational behaviors, and rapport. Methodologically, we will first compute the specific performance metrics relevant to the tasks undertaken by dyads in our study, as described above. In order to associate these metrics to conversational behaviors, rapport level, and IBS, over time, we count the number of hypotheses, and evidence statements supporting those hypotheses, in the read-out session between the children and the experimenter for each week, and we associate these performance metrics to the rapport utopy score for that week, and the mean IBS score for the collaboration phase for that week. Our hypothesis is that while a moderate level of rapport is likely to be beneficial for performance, either too little or too much rapport might hinder task effectiveness. This could be due to an overemphasis on maintaining harmonious interactions at the expense of task focus, or conversely, insufficient rapport leading to poor collaboration. We therefore expect to find a non-linear relationship, potentially inverted U-shaped, between rapport levels and task performance. To test this hypothesis we will employ regression models, including quadratic regression, to test the hypothesized inverted U-shaped relationship. This will enable us to assess the impact of varying levels of rapport on performance metrics while controlling for other variables. Furthermore, we will conduct subgroup analyses to explore if this relationship varies across different dyads, tasks, levels of IBS or ages, or over the 6 weeks of the study. This could involve stratifying dyads based on one of these variables. By integrating performance data, we aim to provide a more nuanced understanding of the role of rapport in collaborative tasks. This kind of analysis may be supplemented by machine learning models such as random forests, where the model is trained on a portion of the data, with the random forests constructing multiple decision trees during the training, and outputting the mean prediction of these trees. In essence this enables the model to recognize complex patterns, such as how different variables interact to affect task performance, thus potentially uncovering intricate relationships such as the hypothesized non-linear relationship between conversational behavior, rapport, and task performance. Techniques of this sort, however, require a significant amount of data as, after training, the model is validated on a separate dataset to assess accuracy. If 176 dyads are collected, the amount of data could be sufficient. The results could have important implications for how rapport is fostered in team settings, particularly in educational and organizational contexts, where performance outcomes are critical. The insights gained from this analysis could contribute to a more comprehensive model of interpersonal dynamics, extending beyond the simple premise that more rapport is always more beneficial.

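### The weekly read-out is called a learning gain but is a single level taken after collaboration, and Claim 4 relates it to rapport with no baseline named

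*Protocol article*

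**What the plan says.** Section 3 (Claim 4) defines productive rapport as "rapport that leads to learning gains in educational tasks, in contrast to unproductive rapport that is detrimental to learning". Section 5.5 repeats a definition based on gains and promises that "we will assess the learning gains of the individuals in each dyad, and the mean learning gain of the dyad, each week" and over the six weeks.

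The weekly instrument is the read-out to an experimenter that closes each session. Section 4.2 gives its purpose as "This phase will serve to assess the children's learning gains after each week". Section 5.5 describes the same read-out differently: it "serves as a metric of performance on each week's work". The only difference score in the plan is the single change from pre-test to post-test, which "will measure learning gains over the course of the 6 weeks for each individual and for the dyad".

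For Claim 4, section 6.4 states: "we count the number of hypotheses, and evidence statements supporting those hypotheses, in the read-out session between the children and the experimenter for each week". These counts are related to the week's rapport utopy score and mean collaboration-phase IBS (inter-brain synchrony), using regression models that include a quadratic one. The other variables to be controlled are not named. Age appears only among the subgroup analyses.

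Every session opens with a solo phase (sections 3 and 4.2): "in the first, solo, phase the children will be asked to describe out loud as much evidence as they can muster". Audio and video run throughout (section 4). Section 5.5 lists only the read-outs and the pre- and post-test for science-reasoning scoring, and Table 1 lists only read-out counts as educational performance.

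**The concern.** The construct is a gain and the analysed weekly outcome is a level. An able or older child can give a high count whatever happened with the partner. The count alone cannot separate what a child brought to the session from what the collaboration added.

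This matters for Claim 4 if what the child brings is also related to rapport. The Introduction raises one such route. Of pupils who put relationship-building ahead of schoolwork, it says: "This is particularly the case for low-performing students, who may wish to distract their peers from collaborative work". Counts are also pooled over ages 5 to 12, and section 6.6 expects reciprocal behaviour and IBS to change with age.

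A rapport-performance association that only reflects starting ability could then be read as productive or unproductive rapport. It could pass into the IBS pattern sought for productive rapport and into the design of the virtual peer.

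**Working it through.** **Which measure is a gain**

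| Measure | When taken | Baseline | Used in section 6.4 |
|---|---|---|---|
| Weekly read-out count | once per session, after collaboration and chat | none named | yes |
| Pre-test to post-test change | before week 1 and after week 6 | pre-test | not mentioned |
| Solo-phase output | each session, before collaboration | could serve as one | not scored |

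The plan gives no error rate or bias figure for Claim 4, so there is none to reproduce. The sizes below are illustrations.

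**Inputs.** From the protocol: 176 dyads (section 4.1). Assumed: ability correlates 0.6 with the count and r = -0.2, -0.3 or -0.4 with rapport; rapport has no true effect; one value per dyad; all variables standardised; a baseline score of reliability 0.6 or 0.8.

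**Formulas.** Spurious correlation without a baseline = 0.6 × r. Rapport coefficient after adjusting for a baseline of reliability k = 0.6 × r × (1 - k) / (1 - k × r²).

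- r = -0.2: unadjusted 0.6 × (-0.2) = -0.12. At k = 0.8: -0.12 × 0.2 / (1 - 0.032) = -0.02. At k = 0.6: -0.12 × 0.4 / (1 - 0.024) = -0.05.
- r = -0.3: unadjusted -0.18. At k = 0.8: -0.18 × 0.2 / (1 - 0.072) = -0.04. At k = 0.6: -0.18 × 0.4 / (1 - 0.054) = -0.08.
- r = -0.4: unadjusted -0.24. At k = 0.8: -0.24 × 0.2 / (1 - 0.128) = -0.06. At k = 0.6: -0.24 × 0.4 / (1 - 0.096) = -0.11.

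**Simulated rejection at two-sided 5%, true effect nil**

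| Test | r = -0.2 | r = -0.3 | r = -0.4 |
|---|---|---|---|
| Linear term, no baseline | 34% | 67% | 90% |
| Linear term, baseline k = 0.8 | 6% | 9% | 14% |
| Linear term, baseline k = 0.6 | 11% | 20% | 33% |
| Quadratic term, no baseline | 5.2% | 4.6% | 5.0% |

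With six weekly values per dyad, each centred on its dyad mean, the linear term rejects in about 5% of runs, because stable ability cancels.

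**What a false inverted U would need.** In a second model (count reliability 0.8), ability was tied to the square of rapport, so that ability is low at both rapport extremes. At correlations of 0.1, 0.2 and 0.3 in size, the quadratic term rejects in 21%, 64% and 93% of runs. A purely linear link leaves it near 5%.

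**Annotation load.** 176 × 2 = 352 children. Scoring every solo phase: 352 × 6 × 10 min = 21,120 min = 352 hours at most. Weeks 1, 3 and 5 only: 352 × 3 × 10 min = 176 hours at most.

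**The case against.** The case on the other side has four parts.

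1. **Wording.** Section 5.5 also calls the read-out a performance metric, and section 6.4 and Table 1 speak of performance throughout. A true pre/post change exists, and section 5.5 intends to relate it to rapport. This stands, and it confines the problem to the weekly measure. Sections 4.2 and 5.5 still promise weekly gains, and section 6.4 does not bring in the pre/post change.

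2. **Covariates.** An article can leave the covariate list to the full plan, and the pre-test is already scored with the same manual. This stands in part. The pre-test is usable, but it resembles only the task of weeks 1 and 2. The list of what is scored is fixed in section 5.5 and leaves out the solo phase.

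3. **Size.** A reader might infer that Claim 4 has a false-positive rate of 34% to 90%, or that low-ability dyads will be taken for unproductive rapport. The documents support neither. Those rates belong to a linear term with one value per dyad and assumed correlations. The Claim 4 hypothesis is an inverted U, and the weekly data give six values per dyad. The Introduction says that low performers may distract their peers. It does not say that their dyads receive higher observer-rated rapport. Talkative children could score high on both, which would reverse the bias.

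4. **The solo baseline.** In weeks 2, 4 and 6 the task repeats, so the solo score already carries the previous week's collaboration. Adjusting for it would remove part of that carried-over effect. This stands and shapes the fix.

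The solo-only control children do not answer the point. They separate collaborating from merely doing the task, and cannot adjust for ability differences among collaborating dyads.

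**Conclusion.** The concern holds in a limited form. The weekly read-out is a level that two sections label a gain, and Claim 4 analyses it with no baseline named although its construct is defined by gains. If ability or age is related to rapport, the linear or between-dyad association can be confounded. Sign and size are unknown. The illustrated correlations of -0.12 to -0.24 rest entirely on the assumed inputs. A linear link does not by itself produce a false inverted U, since the quadratic term stays near 5%. A within-dyad comparison removes stable ability, but the article does not say that one will be used. The six-week pre/post change is not affected. The change is worth making because one baseline is already scored and a closer one is already recorded.

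**What to change.** 1. In sections 4.2 and 5.5, call the unadjusted read-out weekly performance. Reserve learning gain for the pre/post change or a baseline-adjusted result.
2. In section 6.4, condition the weekly count on the pre-test and age group. Model the six weeks as repeated measures within dyad, and separate within-dyad from between-dyad rapport. This needs no new data or scoring.
3. Preferably also score the recorded solo phase with the same manual. Use the solo score from the first week of each task (weeks 1, 3 and 5) as the task-specific baseline, because those of weeks 2, 4 and 6 carry the previous week's collaboration.

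Cost: step 3 takes up to about 352 hours of annotation for all solo phases, or about 176 hours for weeks 1, 3 and 5 only. Some confounding remains after adjustment because any baseline is measured with error. In the illustration, the linear term still rejects in 6% to 14% of runs at reliability 0.8 and in 11% to 33% at 0.6.
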